**5.2.3 Restoration of Sintilimab**

Resuming use of Sintilimab requires that treatment related AEs to return to grade 0-1 or baseline, with an ECOG PS score of 0-1.

**5.2.4 Management of Sintilimab-related infusion reactions**

Sintilimab may cause severe or life-threatening infusion reactions, including severe hypersensitivity or allergic reactions. Signs and symptoms usually appear during the drug infusion or shortly after the infusion, and can usually be managed after the infusion is completed. It can be completely resolved within 24 hours. Guidelines for the management of sintilimab-related infusion reactions are shown in the table below.

| **NCI CTCAE classification** | **Treatment** | **Pretreatment medication during subsequent administration** |
| --- | --- | --- |
| Level 1  Mild reaction; no need to interrupt the infusion; no intervention | According to the patient's medical indications, strengthen the monitoring of their vital signs until the researcher believes that the subject's condition is stable. | no |
| Level 2  Need treatment or interruption of the infusion, symptomatic treatment (such as antihistamines, non-steroidal anti-inflammatory drugs [NSAIDS], anesthetics, intravenous fluids) should be given as soon as possible and a rapid response; preventive medication for ≤24 hours should be taken | Stop the infusion and monitor the symptoms. Other appropriate medications may include but are not limited to: intravenous infusion of antihistamines, NSAIDS, Paracetamol anesthetic  According to the patient's medical indications, strengthen the monitoring of their vital signs until the researcher believes that the subject's condition is stable.  If the symptoms are relieved within one hour after stopping the drug infusion, the infusion can be restarted at 50% of the original infusion rate (for example, reduced from 100 mL/h to 50 mL/h). Otherwise, the medication should be suspended until the symptoms are relieved, and the subject should receive pretreatment medication before the next scheduled dosing.  For subjects who still have Grade 2 toxicity even after receiving adequate pretreatment medication, further study drug treatment should be permanently discontinued. | The following pretreatment medications are acceptable for 1.5 hours (±30 minutes) before Sintilimab:  Oral 50 mg diphenhydramine (or an equivalent dose of antihistamine).  500-1000 mg acetaminophen (or an equivalent dose of antipyretic) is taken orally. |
| Level 3 or 4  Level 3:  Long duration (that is, failure to respond quickly after symptomatic medication and/or short-term interruption of infusion); symptoms relapse after initial improvement; hospitalization is required due to other clinical sequelae (such as kidney damage, lung infiltration)  Level 4:  Life-threatening; requires pressor agents or ventilatory support | Stop the infusion. Other appropriate medications may include but are not limited to: epinephrine**, intravenous infusion of antihistamines, NSAIDS, Paracetamol anesthetic, Oxygen booster drugs, Corticosteroids.  Should strengthen the monitoring of the patient’s vital signs based on the patient’s medical indications until the investigator believes that the subject’s condition is stable.  May require hospitalization.  **If an allergic reaction occurs, epinephrine should be used immediately.  Subjects should permanently stop further study drug treatment. | No follow-up administration |
| Appropriate first aid equipment should be provided in the ward, and the physician should be contacted at any time during the administration period. For further information, please refer to the Common Terminology Standard for Adverse Events (CTCAE) Version 5.0[(Http://ctep.cancer.gov)](http://ctep.cancer.gov/) | | |

**5.2.5 Other permitted dose adjustments of Sintilimab**

In conditions other than treatment-related AEs, such as medical/surgical events or management reasons not related to the study treatment, sintilimab treatment may be discontinued. Subjects should restart the study treatment within 3 weeks after the planned discontinuation of medication, unless there are other discussions with the sponsor. The reason for discontinuing medication should be recorded in the subject’s study record.

**5.2.6 Principles for the treatment of the toxicity of immune-checkpoint inhibitors**

AEs related to sintilimab exposure may be caused by immunological mechanisms. These immune-related AEs (irAE) may occur within a short period of time after the first administration or several months after the last administration of Sintilimab, and may affect more than one body systems at the same time. Therefore, early detection and initiation of treatment is essential to reduce complications. Based on current clinical trial data, most irAEs are reversible and can be managed by interruption of sintilimab, administration of glucocorticoids, and/or other supportive therapies. For suspected irAEs, make sure to perform an appropriate evaluation to confirm the cause or rule out other causes. Other procedures or tests such as bronchoscopy, endoscopy or skin biopsy may be included as part of this assessment. Based on the severity of the irAE, suspend or permanently stop sintilimab treatment and administration of glucocorticoids. The dose adjustment and toxicity management guidelines for potential irAEs can be found in the "Immune-related Adverse Events Management Manual" provided by the sponsor.

**5.2.7 Concomitant therapy**

5.2.7.1 Permitted concomitant treatment

Medications determined by the investigator to meet the requirements of the protocol (for example, for the treatment of disease-related symptoms and concomitant treatment of various AEs related to the treatment). Subjects who need long-term medication due to underlying diseases such as hypertension and diabetes can continue their medication. Local glucocorticoid medications are allowed, such as topical skin application, eye drops, nasal spray, and inhalation. Subjects who routinely take non-steroidal anti-inflammatory drugs (NSAIDs) or salicylic acid drugs (equivalent to 1.3g aspirin per day) should stop the above drugs. Subjects taking long half-life NSAIDs or salicylic acid drugs (such as naproxen, piroxicam, diflunisal, or nalbumetone) need to stop the drugs 5 days before to 2 days after Sintilimab initiation.

5.5.2 Prohibited concomitant treatment

Subjects are prohibited from receiving the following treatments during the treatment period of this study: Biological therapy with anti-tumor effect (except for cytokine drugs used to treat adverse events caused by chemotherapeutic drugs), and proprietary Chinese medicines with anti-tumor effect; Drugs with immunomodulatory effects, including but not limited to non-specific immunomodulators (such as thymosin, interferon, interleukin, immunoglobulin, gamma globulin) and Chinese patent medicines with immunomodulatory effects, etc. Chemotherapy not specified in this regimen. Live vaccination within 30 days before the first administration of Sintilimab and during the study. Live vaccines include, but are not limited to, the following: measles, mumps, rubella, varicella, yellow fever, rabies, BCG, typhoid (oral) vaccine. It is allowed to receive inactivated virus vaccines against seasonal influenza, but it is not allowed to receive live attenuated influenza vaccines for intranasal inoculation. Corticosteroids. Allows the use of inhaled steroids as part of a fixed treatment for asthma or chronic obstructive pulmonary disease (COPD). Allows corticosteroids to be used in the treatment of adverse events with underlying immune causes. After consultation with the sponsor, the use of physiological doses of corticosteroids can be approved. Note: Prophylactic corticosteroids are allowed to avoid allergic reactions (for example, pretreatment prior to administration of intravenous contrast agents or chemotherapy drugs). According to the investigator's assessment, subjects who need to use any of the above treatment methods for clinical treatment should be excluded from the trial. Subjects can receive other medications deemed medically necessary by the investigator. It is important for researchers to review each drug (prescription and over-the-counter) that subjects received before the start of the study and during each study visit. At each visit, the subject must be asked about any new drugs received. In order to reduce the risk of adverse drug interactions, all measures must be taken to limit the number of concomitant medications that are really necessary. During the administration period, you should avoid receiving hepatotoxic drugs (that is, drugs that are warned of hepatotoxicity in the product instructions). Researchers are encouraged to [review each](http://www.livertox.nih.gov/) potential hepatotoxic drug by searching the www.livertox.nih.gov website.

**5.2.8 Drug management**

5.2.8.1 Drug management

The investigational drug in this study is Sintilimab (IBI308). Sintilimab should be refrigerated at 2～8℃, protected from light, and stored in a dry place. Do not freeze. All test drugs are transported to each research center in the cold chain, and should be kept and distributed by special personnel. Test drugs should be stored in a refrigerator that only authorized personnel can open. After receiving the drugs, the investigator should confirm that the drug transportation temperature is within the specified range, sign for receipt after verification, and store at the specified temperature. If the temperature is abnormal during transportation or storage in the research center, the drug should be transferred to the specified temperature as soon as possible, and the subject should not be used for the time being, and reported to in time, and deal with it according to Innovent Biologics’ opinion. All experimental drugs provided by the sponsor can only be used in this experimental study, and shall not be used for purposes other than those specified in this protocol. The investigator must promise not to provide the trial drug to anyone unrelated to the trial. Sintilimab that has been discontinued due to special reasons should be stored under the same storage conditions until the inspector has completed the inventory and check, and arrange for recycling.

5.2.8.2 Drug recovery and destruction

In this study, the used research drug container can be destroyed on the spot according to the applicable guidelines and operating procedures established by the research center and local institutions. All unused research drugs shall be recycled to Innovent Biologics for unified destruction after the research is completed/terminated or after the expiry date.

5.2.8.3 Records of study drugs

The designated personnel of the research center shall make timely records of the receipt, distribution, use, inventory, destruction, recovery, and destruction of research drugs in accordance with the requirements of relevant regulations and guidelines.

**5. 3 GM-CSF**

Commodity name: Terli; Manufacturer: Xiamen Tebao Biological Engineering Co., Ltd.

It starts on the second day after the completion of SBRT treatment (the first day of Sintilimab), and is applied for a total of 14 days. The dose is 125μg/m2. During the period (d1-14), a total of 3 peripheral blood routine checks (d5/9/14) are required. The adverse events and treatment principles are shown in the table below.

| **AEs related to GM-CSF** | **Symptoms** | **Discontinuation and treatment** |
| --- | --- | --- |
| Cold-like symptoms | Fever, fatigue, myalgia, etc. | No need to stop the drug, NSAIDS can be used for symptomatic treatment or preventive use |
| Bone pain | Grade 2 | Suspend dosing and resume dosing after symptoms disappear |
|  | Grade 3-4 | Permanent discontinuation |
| Diarrhea/abdominal pain | Grade 2 | Suspend the administration, symptomatic treatment, resume administration after the symptoms disappear |
|  | Grade 3-4 | Permanent discontinuation |
| Dermatitis | Grade 2 | Suspend the administration, treatment with corticosteroids, and resume administration after the symptoms disappear |
|  | Grade 3-4 | Permanent discontinuation |
| Elevated white blood cells | WBC≥40*10^9/L | Suspend the administration, no therapy, resume the administration after WBC≤10*10^9/L |
|  | WBC≥100*10^9/L | Suspend the administration, orally take hydroxyurea daily 20-30mg/kg or leukocyte apheresis, and resume administration after leukocyte ≤10*10^9/L |
| First-dose reaction | Transient hypoxia  or hypotension | Suspend dosing and resume dosing after symptoms disappear |
| Respiratory distress syndrome | Acute dyspnea, refractory hypoxemia, diffuse infiltrating shadows of both lungs on chest X-ray | Permanently discontinue the drug  give oxygen and glucocorticoid therapy |
| Other conditions that the investigator believes need to be stopped |  | Suspend or permanently discontinue the drug |

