**3.3 Subject withdrawal/discontinuation criteria:**

1. Inappropriate enrollment. Those who have not received any treatment after enrollment should withdraw immediately, and the subject's information will not be included in the study analysis. If the subject has already received study treatment, the investigator will evaluate the subject and determine the benefit and risk of the subject before deciding whether to withdraw. If the subject needs to be excluded, he/she will be withdrawn from the study after the completion of follow-up after treatment. The subject’s information will not be included in the efficacy analysis of this study, but should be included in the safety analysis.
2. Any of the following situations occur during the pre-treatment evaluation stage: new or deteriorated systemic disease which meet the exclusion criteria, voluntarily withdraw consent or lost to follow-up or death; poor compliance.
3. For those who are considered to be excluded by investigators, the investigator shall report the reasons for the exclusion to the principal investigator. When permitted, patients who have not yet received any study treatment should be withdrawn immediately, and the information of this subject will not be included in the study analysis. If the subject has already received the protocol specified treatment, he/she will be withdrawn from this study after the completion of the follow-up after treatment, and the subject will not be included in the efficacy analysis of this study, but should be included in the safety analysis.
4. Subjects may request withdraw from the clinical trial at any time during the study period if they do not want to continue.
5. If serious adverse events occur, the subject might be withdrawn on the judgment of the investigator.
6. Deterioration during the trial, which may threaten the life of the subject, or other conditions that may affect the observation appear during the trial.
7. The subject lost follow-up or die during the treatment period.
8. The subject received chemotherapy, Chinese medicines, other immunotherapy drugs, radiotherapy sensitizers, or other drugs that affect the efficacy and toxicity evaluation during the trial.
9. Serious deviations which makes it difficult to evaluate the drug effect.
10. Poor compliance.
11. **Study plan and timing of procedures**

[figure not shown]

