**6 Statistical analysis**

**6.1 Calculation of sample size**

This study uses the objective response rate (ORR) as the primary end point. This single-arm study requires 56 eligible patients. Considering a 10% dropout rate, a total of 63 patients will be enrolled.

The research hypothesis is based on Checkmate 017 and Checkmate 057 study, which reported an ORR of 20%. If the ORR of the experimental treatment in this study is 20%, it is not worthy of further study. But if the ORR of the experimental treatment in this study is 38%, the study is considered successful. The purpose of this study is to distinguish ORR between 20% and 38%. The statistical assumptions are: the null hypothesis ORR<=20%, and the opposite hypothesis ORR>=38%. If 17 or more of the 56 eligible patients are CR or PR, this study is deemed successful and is worthy of further study. With a one-sided type one error rate (alpha) equal to 0.0432, this study has at least 90% statistical power to reject the null hypothesis.

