**6.5 Study Endpoint**

**6.5.1 Primary endpoint**

**Overall response rate (ORR):** The ratio of the total number of patients achieving CR or PR to the total number of evaluable cases according to the RECIST1.1. The data will be expressed as a two-sided confidence interval.

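### Whether a treated patient given the glucocorticoids that 5.3 orders for GM-CSF respiratory distress syndrome stays in the ORR denominator is left to a discretionary choice made after the toxicity

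*Protocol*

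**What the plan says.** All references are to the protocol.

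- **5.3 (GM-CSF).** For respiratory distress syndrome, the toxicity table stops GM-CSF permanently and says to "give oxygen and glucocorticoid therapy". It gives no route and does not say that the patient leaves the trial.
- **5.2.7.1 (permitted treatment).** Drugs that meet the protocol's requirements are allowed, with "concomitant treatment of various AEs related to the treatment" among the examples.
- **5.5.2 (prohibited treatment).** Corticosteroids are on the list. The exceptions are inhaled use for asthma or COPD, physiological doses approved after consulting the sponsor, allergy prophylaxis, and this one: "Allows corticosteroids to be used in the treatment of adverse events with underlying immune causes". The paragraph then says that, on the investigator's assessment, "subjects who need to use any of the above treatment methods for clinical treatment should be excluded from the trial".
- **3.3 item 3.** When the investigator thinks a patient should be excluded, "the investigator shall report the reasons for the exclusion to the principal investigator". If that patient has already been treated, "the subject will not be included in the efficacy analysis of this study, but should be included in the safety analysis".
- **3.3 item 5.** After a serious adverse event the investigator may withdraw the patient. Nothing is said about the efficacy analysis.
- **6.5.1.** ORR is "The ratio of the total number of patients achieving CR or PR to the total number of evaluable cases".
- **6.1.** The trial succeeds with 17 or more responders among 56 patients. "Considering a 10% dropout rate, a total of 63 patients will be enrolled".

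**The concern.** Section 5.3 orders a drug class that 5.5.2 lists as prohibited, and neither section refers to the other. The immune-cause exception may or may not cover lung toxicity from GM-CSF, and the protocol does not say which. A site can therefore give the steroid and keep the patient, or give it and conclude that the patient should be excluded.

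The second course matters for the primary endpoint. This is an open-label, single-arm trial with investigator-assessed response, and its denominator is evaluable cases. A patient excluded under 3.3 item 3 leaves that denominator, while for one withdrawn under item 5 no removal is stated. Two patients with the same toxicity and the same treatment could be counted differently, and the choice is made once the toxicity is known. Patients lost to severe early toxicity may well have no documented response, so dropping them tends to raise the reported ORR.

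**Working it through.** **Step 1. Reproduce the design in 6.1.** The inputs are n = 56, cutoff 17, null ORR 20%, alternative ORR 38% and dropout 10%. The formula is the exact binomial tail, P(X ≥ 17 | n, p) = Σ C(n,x) pˣ (1−p)ⁿ⁻ˣ for x from 17 to n.

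- n = 56, p = 0.20: 0.0432, as stated.
- n = 56, p = 0.38: 0.9076, in line with the stated power of at least 90%.
- 56 / (1 − 0.10) = 62.2, rounded up to 63, as stated.

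**Step 2. Trace one patient through the text.** Suppose a patient on GM-CSF (days 1 to 14) develops respiratory distress syndrome.

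1. 5.3 requires glucocorticoids. For refractory hypoxemia the natural reading is systemic use, so the allowance in 5.2.7.1 for local steroids does not help.
2. If the event is judged immune-caused, 5.5.2 allows the steroid and the matter ends.
3. If it is not, none of the other exceptions in 5.5.2 fits, and its exclusion sentence can be applied. 5.2.7.1 still supports treating the event, and no order of precedence is given.
4. If the investigator goes on to exclusion, 3.3 item 3 takes the patient out of efficacy. If the investigator uses item 5 instead, no removal is stated.

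The link from 5.5.2 to item 3 comes from reading the two rules together. Neither cites the other, and item 3 also needs a report to the principal investigator.

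**Step 3. Size.** The documents give no rate for this event, so the number removed is assumed to be 1 or 2. The cutoff stays at 17.

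| Assumption | Quantity | None removed | 1 removed | 2 removed |
| --- | --- | --- | --- | --- |
| (a) Removal unrelated to response, not replaced (n = 55, 54) | Type I error at 20% | 0.0432 | 0.0367 | 0.0310 |
| (a) as above | Power at 38% | 0.9076 | 0.8905 | 0.8709 |
| (b) Only non-responders removed, not replaced | Reported ORR with 17 responders | 17/56 = 30.36% | 17/55 = 30.91% | 17/54 = 31.48% |
| (c) Only non-responders removed, replaced up to 56 | Type I error at 20% | 0.0432 | 0.0505 | 0.0585 |

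In (b) the number of responders does not change, so the type I error stays at 0.0432. Only the reported proportion moves, by 0.55 or 1.12 percentage points. In (c), 57 or 58 patients are treated to obtain 56 analysed, so the error is P(X ≥ 17 | 57, 0.20) or P(X ≥ 17 | 58, 0.20).

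**The case against.** The strongest reply is that there is no real conflict. 5.5.2 itself allows steroids for immune-caused events. GM-CSF is given here as an immune stimulant next to an anti-PD-1 antibody, so acute lung toxicity could reasonably qualify. 5.2.7.1 permits treatment of related events, and a specific toxicity order normally prevails over a general medication list. The list also names immunomodulatory drugs, which read literally would cover the trial's own GM-CSF, so it is evidently aimed at treatment from outside the protocol.

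Much of this stands. A reader might infer that 5.5.2 flatly bars the steroid that 5.3 orders. The text does not support that, because the immune-cause allowance and 5.2.7.1 both offer a way through. What remains is an exception that the protocol never reconciles with its own order, with an exclusion sentence attached.

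The second reply is that removal from ORR needs a chain of events: a probably rare toxicity, a judgment that it is not immune-caused, and a choice of item 3 over item 5. Item 8, on drugs that affect evaluation, likewise states no removal. Also, GM-CSF ends on day 14 while efficacy is first assessed after three courses, about week 9, so the choice would ordinarily come before response is known. This stands too, and it limits the size. It does not remove the point: item 3 as written lets a treated patient leave the efficacy analysis on an exclusion that the investigator initiates, after a toxicity is known.

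**Conclusion.** The point holds in a limited form. The steroid wording alone is a minor clarification. The more solid part is that 3.3 item 3 can drop a treated patient with severe toxicity from the ORR denominator, while item 5 states no such removal.

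The expected effect is small, and no figure in 6.1 is wrong. A reader might infer that the trial's type I error is inflated. That does not follow: without replacement the error stays at 0.0432 or falls, and it rises only under (c), which needs every removed patient to be a non-responder and a replacement rule that the protocol does not contain. The illustration rests on an assumed one or two removals. Topical steroids and events judged immune-caused fall outside the point.

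**What to change.** 1. **Main change, in 3.3.** State that eligible patients who received study treatment stay in the ORR denominator when they are withdrawn or excluded because of toxicity or its protocol-directed treatment. They count as non-responders if no response is documented.
2. **Minor clarification, in 5.5.2.** Add an exception for corticosteroids given under the toxicity rules of 5.2 and 5.3. Which drugs and routes it covers is for the clinical team.

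Both are wording changes, and the sample size and cutoff stay as they are. The price is a possibly slightly lower reported ORR: in the illustration, 30.4% instead of 30.9% or 31.5%.
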